#### Participant timeline

The study schedule, including enrolment, intervention, and data assessment, is shown in Fig. 1. Enrolled participants will receive an initial mental distress screening (NCCN Distress Thermometer). Individuals who report a distress score $$\ge 5$$ will complete further baseline questionnaires and a video-based diagnostic interview to complete the SCID. Individuals who report a distress score $$< 5$$ will be excluded from further participation. Once the presence of a mental disorder has been verified on the basis of this diagnostic interview, the participants will be randomly assigned to one of the two study arms. Individuals excluded according to the distress thermometer or SCID will receive information about possible contact points in the event of future cancer-related distress.

All participants will then have a first appointment with their randomly assigned consultant. If the participants are assigned to the intervention group, the first manualised intervention session will be conducted. If the participants are assigned to the control group, a supportive talk including feedback on the diagnosis and two further supportive talks will be provided.

Surveys using the above-mentioned standardised instruments will take place at five measurement points (before, during and directly after the intervention as well as 6 months after the intervention). Questionnaires for process evaluation (ZUF-8, WAI-SR) will be administered at the two interim measurements after the fourth and eighth sessions in the VA-V group. The measurements will take place online via the ViVA platform, and the participants will be reminded to complete the questionnaires. It is important for the project that the participants will respond as soon as possible (preferably within 1–3 days). The ViVA platform will send a reminder after 3 days and again after 6 days.

#### Sample size

Following the guidelines for psycho-oncological diagnostics [5], the Hospital Anxiety and Depression Scale (HADS) is defined as the primary endpoint for testing the effectiveness of the intervention. For the sample calculation, a mean effect of $$d = 0.5$$ of the VA-V versus the active control is assumed to be clinically relevant. This assumption is based on a review of the effects of psycho-oncological interventions compared to those of controls [36]. The sample size was calculated using SampSize (epiGenesys. A University of Sheffield company https://app.sampsize.org.uk). For the superiority hypotheses, an $$\alpha$$-error probability of .05, a power of $$1- \beta = .80$$, a mean effect of $$d = .5$$ (standardised mean difference), and a population $$SD = 1$$ (also standardised) are assumed. SampSize is used to calculate the sample size for a superiority trial with a parallel design and normally distributed outcome [37]. This results in $$n = 51$$ per group as a minimum requirement. Based on an estimated dropout rate of 30 % (e.g. [38]), $$n = 73$$ participants per group will be required. We aim to include $$n = 146$$ participants in the trial.

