**Methods:**

This trial will use covariate-adaptive randomisation according to gender and type of tumour disease to assign participants to one of two study arms (value-oriented behavioural activation consisting of 12 manualised follow-up sessions delivered via video consultation vs. S3-Guideline-compliant aftercare comprising three supportive talks). Psychological strain, psychosocial distress, quality of life, work-related outcomes, fear of cancer recurrence, goal adjustment, satisfaction with the consultant-participant relationship, and rumination will be measured at baseline, twice during treatment, posttreatment, and at the 6-month follow-up. The target sample of 146 tumour patients experiencing high psychosocial distress will be recruited at the Rehazentrum Oberharz, Germany.

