## Methods/design

### Trial design

This study is a nonblinded two-armed parallel randomised controlled trial (see Additional File 1 for the SPIRIT checklist). The superiority of the VA-V over the German S3-Guideline-based intervention will be evaluated. Participants will be randomly assigned to either the VA-V group or the German S3-Guideline-compliant aftercare group. Random allocation will be performed on a 1:1 ratio basis and covariate-adaptively for gender and type of tumour disease. The assessments will be conducted at baseline (T1), during the intervention (T2, T3), postintervention (T4), and at the 6-month follow-up (T5; see Fig. 1). The VA-V group will receive 12 online intervention sessions. The control group will be an active control group receiving 3 supportive online talks according to the German S3-Guideline [5].

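### The 51 per group behind the target of 146 is a one-sided 5% figure, and the protocol never says so; under a two-sided 5% test the unadjusted power with 51 completers per group is about 71%

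*Protocol article*

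**What the plan says.** The sample size section of the protocol article names the HADS as the primary endpoint and lists the planning inputs: "For the superiority hypotheses, an $$\alpha$$-error probability of .05", power of .80, "a mean effect of $$d = .5$$ (standardised mean difference") and "a population $$SD = 1$$ (also standardised) are assumed". The software routine is described as one for "a superiority trial with a parallel design and normally distributed outcome". The result is "This results in $$n = 51$$ per group as a minimum requirement", which is raised to 73 per group for an expected 30% dropout, 146 in all. The abstract repeats that total ("The target sample of 146 tumour patients experiencing high psychosocial distress will be recruited at the Rehazentrum Oberharz, Germany"), and the Recruitment section closes enrolment once it is reached.

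On direction, the Trial design section says "The superiority of the VA-V over the German S3-Guideline-based intervention will be evaluated", and the Background states the primary objective as lower distress under VA-V. The Statistical methods section describes an intention-to-treat multilevel structural equation model with maximum-likelihood handling of missing values. None of these places, nor any other in the article, says whether alpha or the primary test is one- or two-sided.

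**The concern.** Alpha has no fixed meaning in a power calculation until its sidedness is given. It is the one input missing from an otherwise complete list, and it decides whether the answer is 51 or 64 per group. Most readers will take an unqualified .05 for a superiority trial as two-sided, and on that reading 51 per group does not deliver 80% power in the comparison that was calculated.

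Two things are at stake. If the result is reported with a two-sided p-value or a 95% CI, an unadjusted analysis of 51 completers per group would miss a true effect of d = 0.5, which the protocol calls clinically relevant, 29% of the time rather than 20%. If a one-sided 5% test is meant, the chance of wrongly declaring VA-V superior is twice the conventional 2.5%. A sidedness left open until the data are in also leaves the type I error rate open.

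**Working it through.** **Inputs, all from the Sample size section except the allocation ratio.** Alpha .05; power .80; d = 0.5; SD = 1; parallel groups, normal outcome; dropout 30%; 1:1 allocation (Trial design).

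**Method.** Two-sample t-test with n per group: degrees of freedom 2n − 2, noncentrality d·√(n/2). Power is the probability that the noncentral t exceeds the critical value t(1 − .05) one-sided or t(1 − .05/2) two-sided; the two-sided case adds the negligible opposite tail.

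**Step 1: reproduce the plan's figure.** At n = 51 the noncentrality is 0.5·√25.5 = 2.525 with 100 degrees of freedom.

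| n per group | One-sided .05 | Two-sided .05 |
|---|---|---|
| 50 | 79.9% | 69.7% |
| 51 | 80.6% | 70.6% |
| 63 | 87.4% | 79.5% |
| 64 | 87.9% | 80.1% |
| 73 | 91.3% | 85.1% |

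The smallest n reaching 80% is 51 one-sided and 64 two-sided. The stated 51 is therefore exactly the one-sided answer.

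**Step 2: rule out the choice of approximation.** The normal formula n = 2(z₁₋α + z₁₋β)²/d² gives:
- one-sided: 2(1.645 + 0.842)²/0.25 = 49.5, so 50;
- two-sided: 2(1.960 + 0.842)²/0.25 = 62.8, so 63.

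The method moves the answer by one patient per group. The sidedness moves it by 13.

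**Step 3: dropout.** 51/0.70 = 72.9, so 73 per group and 146 in total, as stated. The same step from 64 gives 64/0.70 = 91.4, so 92 per group and 184 in total.

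**Step 4: what 51 completers per group give under a two-sided .05 test, unadjusted.** Power for d = 0.5 is 70.6%, so the false-negative risk is 29.4%. Power reaches 80% at d of about 0.56.

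**Step 5: dependence on dropout.** If all 73 per group are evaluable, two-sided power is 85.1%. It stays at 80% or above while at least 64 of 73 are evaluable, a loss of up to 9/73 = 12%. At the plan's own 30% it is about 71%.

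**Step 6: what baseline HADS could add.** Adjusting for baseline with baseline–outcome correlation r raises the effective effect size to d/√(1 − r²). The protocol gives no such correlation, so every r here is an assumption. Two-sided .05, 51 per group:

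| Assumed r | d/√(1 − r²) | Power |
|---|---|---|
| 0.40 | 0.546 | 77.9% |
| 0.45 | 0.560 | 80.0% |
| 0.50 | 0.577 | 82.3% |
| 0.60 | 0.625 | 87.8% |

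**The case against.** The strongest reply is that nothing was miscalculated. The hypothesis is directional throughout, a one-sided 5% test fits that wording, and under it both 51 and the stated 80% are right. This stands as far as it goes: a reader might infer an arithmetic slip, or that the 80% is simply false, and the document supports neither. But superiority names the hypothesis, not the way alpha is split; superiority trials are routinely tested two-sided at 5%. The wording permits a one-sided test without declaring one.

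A second reply is that 71% is pessimistic for the planned analysis. This also largely stands. The figure describes an unadjusted, single-time-point comparison of 51 completers per group. The Statistical methods section plans a multilevel maximum-likelihood model, HADS is measured at T1, T4 and T5, and participants who stop the intervention are still asked to complete questionnaires. The trial's actual power may well be higher, so it would be wrong to read 71% as the power of the trial. What does not stand is using this gain to support the stated 80%: the calculation draws on no correlation and no partial data, and the only predictors the Statistical methods section names for the model are diagnosis and gender.

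A third reply is that sidedness can be left to an analysis plan that is not shown. That is fair for the reporting of the primary test. It is not fair for an input to a published calculation, and a two-sided analysis plan would not match the published basis for 80%.

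**Conclusion.** The point holds as an undeclared assumption behind the stated power, not as a calculation error. The 51 per group, and hence the target of 146, rests on a one-sided alpha of .05. If the primary test is two-sided at .05, power for d = 0.5 is about 71%, assuming an unadjusted comparison and the plan's 30% dropout. It rises to about 85% with no dropout, and to 80% or more with 51 per group if the baseline–outcome correlation is about 0.45 or higher, a value the protocol does not supply. If one-sided 5% is intended, the stated power is right and the 5% false-positive rate in favour of VA-V needs to be declared.

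A reader might also infer that 184 patients must now be recruited. That does not follow: 184 is what an unadjusted two-sided design would need, and the planned analysis can use the baseline HADS already being collected. This should be fixed, but it does not undermine the design.

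**What to change.** In the Sample size section, state that n = 51 per group was derived with a one-sided alpha of .05. Then take one of two routes before outcome data are analysed.

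- **Preferred.** Fix the primary test as two-sided at .05 with a 95% CI. Restate unadjusted power as about 71% for d = 0.5 (80% for d of about 0.56) with 51 completers per group. Specify the primary contrast as adjusted for, or jointly modelling, baseline HADS. Give its power over a range of correlations labelled as assumptions: about 78% at 0.4, 80% at 0.45, 82% at 0.5 and 88% at 0.6.
- **Alternative.** Declare the one-sided 5% test, say that its false-positive rate in favour of VA-V is 5%, and carry it into the analysis and the reporting.

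The cost is wording in the sample size and statistics sections. The target of 146 can stay, with no added patients or assessments. The only downside of the preferred route is a less favourable stated unadjusted power.

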#### Recruitment

Participants are recruited at the Rehazentrum Oberharz Clausthal-Zellerfeld, Lower-Saxony, Germany, by university staff. The recruitment process will be supported by clinic staff (e.g. scheduling the information session on the patients’ calendar). Short presentations in a group setting will introduce patients to the study. The planned recruitment start date is 23 October 2023. The target sample size is $$n = 146$$. After reaching this sample size, recruitment is completed. If the target sample size is not reached, recruitment will be discontinued on 31 December 2024.

Potential participants will receive verbal information about the study project as well as written study information with a data protection declaration, information on video recordings, and two copies of the consent form (see Additional Files 2 and 3). The study information also explicitly states that people without relevant psychosocial distress cannot participate in the study and that participants in the German S3-Guideline group receive supportive talks but no intervention sessions of value-based behavioural activation. The signed consent form, including consent to videography of diagnostic and treatment appointments as well as the data protection declaration, will be a prerequisite for participation in the study. The participants will be informed that the videography will serve the purpose of quality assurance. Any further evaluation of the video material for research purposes will only take place if the participants expressly agree to this point separately in the declaration of consent. Consent forms will be signed by both the participant and the recruiting person, with one copy remaining with the participant. Any questions that may arise can be posed during the information event or afterwards via the contact details of the study staff provided on the information material. Participants will receive their personal access data to the ViVA platform via the contact details they have provided.

### Assignment of interventions

#### Sequence generation

Sequence generation will be achieved through covariate-adaptive randomisation according to gender (male, female, diverse) and type of tumour disease (4 types: breast, gastrointestinal, gynaecological and urogenital, other) by using an interactive web response system. All tumour types of diverse persons will be combined in one category due to the low expected sample size. Male breast cancers will be assigned to the category *other tumours* due to the low expected sample size. Information for this covariate adaptive randomisation will be collected at the baseline measurement through the PO-Bado-KF [34]. To achieve covariate adaptive randomisation, the first 36 individuals out of 143 (25 %) will be allocated completely at random. Starting with participant 37, allocation will be conducted by minimisation [39, 40].

#### Allocation concealment mechanism

To achieve allocation concealment, covariate-adaptive randomisation will be automated through an interactive web response system on the ViVA platform. Allocation will take place after the baseline assessment and diagnostic interview. The project staff cannot predict the randomisation result. The programming will be conducted by an external service provider (Consulting Partner Hannover GmbH).

#### Implementation

The allocation sequence will be generated as described above by an external service provider (Consulting Partner Hannover GmbH). Participants will be enrolled by project staff. The interactive web response system on the ViVA platform will assign participants to interventions.

#### Blinding

Participants cannot be blinded to their allocation since psychosocial interventions are identified naturally for both patients and counsellors. Baseline assessment will be conducted prior to allocation to minimise possible bias.

### Data collection, management, and analysis

#### Data collection methods

Invitations and reminders for the questionnaires will be sent by e-mail and/or SMS. In addition, the diagnostic interview and all sessions in the VA-V will be videographed. The videography of the diagnostic interview will be used for quality assurance. The research data and videographies used for this study will be stored for a period of 10 years in the Department of Clinical Psychology and Psychotherapy at the University of Hildesheim. The written consent forms will also be stored for 10 years. Contact data will be deleted after 36 months. Participants who discontinued the interventions will be asked to nevertheless respond to the remaining questionnaires. The reasons for drop-out will be assessed.

With the help of the ViVA platform, the data collection will be automated. The technical basis is the open-source software Limesurvey on the Linux Apache MySql server. In addition, fear of cancer recurrence will be recorded daily over 10 days with a separate platform on which the German translation of the FCR7 will be implemented. The platform will technically and in terms of data protection be identical to the ViVA platform. The data records will be linked via the participant code.

#### Data management

The data management plan was published on the German Clinical Trial Register website of this trial and will be updated every 6 months. Each participant consent form will be marked with a participant code. The consent form with contact details will thus allow for an assignment of personal data and code. Further data (from the ViVA platform, FCR platform, SCID interview, and videography) will be marked with this participant code and stored separately from the personal data. Thus, all the data intended for scientific evaluation will be stored exclusively in pseudonymous form. The data will, therefore, be de facto anonymous after deletion of the personal data at the end of the trial. Participants will have the right to request the deletion of personal data necessary for scientific evaluation without giving reasons, before the study is completed.

After the deletion of the personal data at the end of the study, deletion will no longer be possible, as the data will be de facto anonymous. Publication of the raw data is not intended. For ethical reasons, the raw data will only be available upon request. Interested researchers will be able to apply to the corresponding author of the study publication for access to the data. All requests will be reviewed by the data protection officer of the University of Hildesheim.

#### Statistical methods

The statistical evaluations for the analysis of the superiority of the VA-V will be carried out as an intention-to-treat analysis via multilevel structural equation models (measurement points nested in persons). Missing values will be estimated using the maximum likelihood method (expectation-maximisation algorithm). The stratification variables (diagnosis and gender) will be considered predictors. To check whether the intervention is implemented as planned, a process evaluation will be conducted, and fidelity will be recorded. In this context, treatment satisfaction and the assessment of the therapeutic relationship, as well as various parameters, such as dropout rates, will be considered. In addition, the predictive significance of participant characteristics (e.g. goal adjustment, treatment satisfaction) for therapy success (HADS) or discontinuation will be determined via regression analyses.

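### The primary model is not stated to condition on baseline HADS or to equalise the arms' T1 means; fixing this is free and worth about 9 points of power at an assumed correlation of 0.5

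*Protocol article*

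**What the plan says.** Table 2 schedules HADS at T1, T4 and T5. T1 precedes allocation in every participant; the Blinding section says "Baseline assessment will be conducted prior to allocation to minimise possible bias". Under Statistical methods, superiority is tested by intention to treat with "multilevel structural equation models (measurement points nested in persons"), and missing values are handled by maximum likelihood. On covariates the section says "The stratification variables (diagnosis and gender) will be considered predictors".

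It does not say whether T1 HADS is a covariate or one of the repeated outcomes. If it is an outcome, the section does not say whether the arms share a mean at T1.

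The Sample size section treats the comparison as a plain two-group contrast: "SampSize is used to calculate the sample size for a superiority trial with a parallel design and normally distributed outcome". It assumes "a mean effect of $$d = .5$$ (standardised mean difference), and a population $$SD = 1$$ (also standardised) are assumed", with no allowance for baseline.

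**The concern.** A pre-randomisation measurement of the primary outcome is usually the most useful covariate available, and here it is collected from everyone at no extra cost. The predictors that the section names leave it out. Placing T1 among the measurement points does not by itself recover the benefit. In the usual model with group, time and group-by-time terms, the arm means at T1 are free, and the interaction at T4 is a difference in change scores.

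Two things are at stake. One is precision. The other is sensitivity to a chance baseline difference δ between arms, since allocation balances gender and tumour type but not HADS. In expectation such a difference enters a post-score comparison as ρδ and a change-score comparison as −(1−ρ)δ. At ρ = 0.5 that is +δ/2 and −δ/2. Conditioning on T1 removes it.

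**Working it through.** **Inputs.** From Sample size: d = 0.5, SD = 1, α = .05, target power 80%, 51 per group analysable, 30% dropout, 73 per group enrolled. The section does not state whether the test is one- or two-sided. The correlation ρ between T1 and T4 HADS is not in the protocol; it is assumed to be 0.5, with a range of 0.3 to 0.7.

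**Reproducing the plan's figure.** A two-sample t-test at one-sided .05 first reaches 80% power at 51 per group. At two-sided .05 it needs 64. Dropout: 51 / 0.7 = 72.9, so 73. The plan's number is therefore a one-sided calculation, and one-sided power is the main yardstick below.

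**Variance factor v for the T4 contrast**, relative to the unadjusted post score, with equal variances:

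- T1 left out: v = 1
- T1 as a repeated outcome with free arm means: v = 2(1−ρ)
- T1 as a covariate, or equal T1 means: v = 1−ρ²

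The last is never larger than the others: 1 − (1−ρ²) = ρ² ≥ 0, and 2(1−ρ) − (1−ρ²) = (1−ρ)² ≥ 0.

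**Power.** Noncentral t with 2n−2 degrees of freedom and noncentrality (0.5/√v)·√(n/2). At n = 51 and ρ = 0.5:

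- v = 1 (both alternatives, since 2(1−0.5) = 1): 0.5 × √25.5 = 2.52, power 80.6%
- v = 0.75: 0.577 × √25.5 = 2.92, power 89.4%

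One-sided power (%), 51 per arm:

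| ρ | T1 left out | Free T1 means | Conditioned on T1 | Gain vs left out | Gain vs free means |
|---|---|---|---|---|---|
| 0.3 | 80.6 | 68.2 | 83.7 | 3.2 | 15.5 |
| 0.4 | 80.6 | 74.0 | 86.2 | 5.7 | 12.2 |
| 0.5 | 80.6 | 80.6 | 89.4 | 8.9 | 8.9 |
| 0.6 | 80.6 | 87.7 | 93.2 | 12.6 | 5.5 |
| 0.7 | 80.6 | 94.4 | 96.9 | 16.3 | 2.5 |

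Gains are taken before rounding. With all 73 per arm observed and ρ = 0.5, power is 91.3% against 96.6%, about 5 points. On a two-sided test with 51 per arm and ρ = 0.5 it is 70.6% against 82.3%, about 12 points.

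**Cross-check.** A generalised least squares calculation for T1, T4 and T5 with a common correlation gives the same pattern under a normal approximation (one-sided, 51 per arm). With free T1 means power is 68.8%, 81.1% and 94.7% at ρ = 0.3, 0.5 and 0.7. With equal T1 means it is 84.2%, 89.8% and 97.1%. The equal-means model therefore matches covariate adjustment.

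**The case against.** A reader might infer that the plan uses diagnosis and gender as its only predictors, ignores baseline HADS, and so gives up 9 to 12 points of power. The protocol does not support that, for four reasons.

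- The predictor sentence is not exhaustive. It names neither treatment group nor time, so taken as a full list it would leave no treatment effect to test.
- Nesting measurement points in persons most naturally includes T1, which the protocol counts among its five measurement points. Leaving T1 out is possible but is the less natural reading.
- A common baseline mean is neither stated nor excluded. If that is the intention, nothing is lost.
- The 12-point figure belongs to a two-sided test, which does not reproduce n = 51, and ρ = 0.5 is the reviewer's assumption.

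It is also fair that 51 per arm assumes the full 30% dropout, whereas participants who discontinue will still be asked for their questionnaires. At ρ = 0.5 the plan meets its 80% target on its own calculation without any adjustment. Not balancing HADS in the allocation, and taking no credit for baseline in the sample size, are acceptable conservative choices.

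The further argument, that an article may leave model detail to a fuller document, carries less weight. The section does state its model and some of its predictors, and the change asked for is a better use of data already collected, not just fuller reporting. What stands of the objection is that the gain is conditional on the model intended.

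**Conclusion.** The point holds in a conditional form. The Statistical methods section does not commit the primary model to conditioning on T1 HADS or to equal T1 means, and two of the models that it permits are less efficient than the data allow. On the one-sided calculation behind n = 51, the gain from committing is about 9 points at ρ = 0.5. Over ρ from 0.3 to 0.7 it is about 3 to 16 points against a post-score analysis, and about 15 down to 2.5 points against a free-baseline model. It is zero if a common baseline mean is already meant.

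The free-baseline model also falls below the planned 80% when ρ is under 0.5 (74.0% at 0.4, 68.2% at 0.3). The conditioned model stays above 80% throughout the range.

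These figures rest on the assumed ρ, equal variances, d = 0.5 and 51 analysed per arm. None of the permitted models is invalid; the loss is one of precision. The principle extends to the other outcomes measured at T1, but these power figures do not: their correlations are unknown, their schedules differ, and the work-related measures (WAI-r, ERA) apply only to participants who are not retired.

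**What to change.** Add one sentence to Statistical methods, before the data are analysed, committing the primary model to one of two forms:

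- T1 HADS as a person-level covariate, with a T1-by-time term, and T4 and T5 HADS as the repeated outcomes; or
- T1 HADS kept in the outcome vector with the two arms' T1 means constrained to be equal, so that the group effect enters only at T4 and T5.

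Keep the allocation factors as predictors, and apply the same rule to every other outcome measured at T1. The cost is one or two degrees of freedom. No new data, visits or participants are needed, and the sample size can stay as it is. T1 precedes allocation, so the adjustment introduces no post-randomisation bias. It also removes a later choice between models that could give different answers.
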